#### Safety outcomes

The results of a routine blood test, routine urine test, routine stool test, renal function test and electrocardiogram are assessed before and after the treatment to ensure the safety of this study. Further more, a urine pregnancy test or serum human chorionic gonadotropin test must be done before enrolling a women patient of childbearing age.

#### Data monitoring board

Two supervisors who are not members of the end-point committee should be assigned to contact and visit the researchers regularly to supervise the trial progress. Through this monitoring process, it can be ensured that it is conducted, recorded and reported in accordance with the protocol and standard operating procedures. In addition, the researchers should agree to cooperate with the supervisors to ensure that any problems found and resolved.

#### Ethics, consent and permission

Written informed consents will be obtained from all patients before enrollment. The study is being conducted in accordance with the Declaration of Helsinki (2008) [14] and has been approved by the ethics committees of Guangdong Provincial hospital of Chinese medicine. In addition, the study is registered with the Chinese Clinical Trial Registry (ChiCTR-OOC-15006155).

#### Sample size and statistical methods

This prospective study is intended to evaluate the efficacy and safety of the combination treatment of SGJP Decoction and steroid standard therapy on AIH. Since there is still no enough reliable data to accurately calculate the sample size for our study, 20 hepatology experts in Chinese medicine or integrative medicine with more than 20 years clinical experience were asked for advice. After two rounds of meetings with these experts, we agreed that 110 patients should be sufficient to gather enough information in order to plan such a clinical trial. And 132 cases are needed if there is a dropout rate of 15%.

The statistical analysis for this study will be performed using SPSS software version 19.0 (SPSS Inc., Chicago, IL, USA). Data will be presented as mean and standard deviation, or frequency and percentages. Comparisons will be conducted between the case group and the control group, also between pre-treatment and post-treatment in each group. For normally distributed variables, means will be compared by using t-tests (two-tailed), and nonparametric variables will be analyzed using Pearson chi-squared tests or Fisher exact tests. All *P*-values will be two-tailed. A P-value of less than 0.05 will be considered statistically significant.

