**Methods:**

A prospective non-randomized study on AIH will be conducted between October 2015 and June 2017 in Guangdong Provincial hospital of Chinese medicine. Eligible AIH patients will be classified as the case group (*n* = 66) and the control group (*n* = 66) based on the interventions. Patients taking Shu-Gan-Jian-Pi Decoction combined with prednisone and azathioprine will be in the case group and those taking prednisone and azathioprine will be in the control group. The whole study will last 48 weeks, including a 24-week observation period and a 24-week follow-up period. The primary outcome was complete response to therapy, defined as complete biochemical remission at the patient’s last visit of observation period and the absence of predefined steroid-specific side effects throughout treatment.

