## Background

Autoimmune hepatitis (AIH) is characterized by acute or chronic liver inflammation, which is considered to be associated with autoimmune response in liver cells. Previous studies [1] have proved that AIH can easily progress to cirrhosis or liver failure, and even some patients need for liver transplantation finally. It is reported that 40% of untreated severe AIH patients might die within 6 months, and those surviving commonly develop cirrhosis and subsequent complications of portal hypertension [2]. Moreover, it accounts for 2.6% of the transplantations in Europe [3] and 5.9% in the United States [4]. Due to this poor prognosis and the increasing detection rate, more and more studies focus on the management of AIH recently. It is well known that low dose prednisone plus azathioprine is the standard therapy for AIH, with alleviation of symptoms achieved in 60 to 80% of cases [5]. However, it must be noted that 50 to 86% of patients witness a recurrence of the disease after stopping medications, while 13% of patients stop the treatment too early due to the severity of the side effects and 9% of patients’ situation will deteriorate, even though they are administered medications according to guidelines [6]. Due to the high recurrence rate and the common side effects of corticosteroids, more and more AIH patients seek for traditional Chinese medicine (TCM) to manage their symptoms and reduce the side effects of corticosteroids in China.

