## Methods/design

### Study design

This is a prospective, non-randomized, controlled study. One-hundred and thirty two AIH patients visited in Guangdong provincial hospital of Chinese medicine at the first time will be enrolled and divided into two groups with a case: control ratio of approximately 1:1. While patients in the control group received the steroid standard therapy, patients in the case group are treated with combination treatment of SGJP decoction and the steroid therapy. Both of the treatment and follow-up period will be for 24 weeks. The details of the flow chart of this trial are shown in Fig. 1.

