### Inclusion criteria

(1) All the patients had either a first diagnosis of AIH or were experiencing relapse after a previous diagnosis of AIH based on histology findings within 12 months before screening. (2) TCM syndrome type: liver stagnation and spleen deficiency. (3) Patients fulfill indications for treatment: serum aspartate aminotransferase (AST) ≥ 10-fold upper limit of normal (ULN) levels; or Serum AST ≥ 5-fold ULN and gammaglobulins ≥ twice ULN; or Bridging necrosis or multiacinar necrosis on histopathological examination (4) aged from 18 to 65 years.

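### Pre/post significance tests within each group cannot separate a decoction effect from the shared steroid therapy, yet they carry the same P<0.05 rule as the between-group comparison

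*Protocol article*

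**What the plan says.** The section on sample size and statistical methods plans two kinds of comparison: "Comparisons will be conducted between the case group and the control group, also between pre-treatment and post-treatment in each group". It then applies one rule to every test: "All *P*-values will be two-tailed", and "A P-value of less than 0.05 will be considered statistically significant". The tests named are t-tests, Pearson chi-squared tests and Fisher exact tests. Nothing in the section marks the within-group tests as descriptive or secondary.

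On treatment, the study design section says that "patients in the case group are treated with combination treatment of SGJP decoction and the steroid therapy", while controls receive the steroid therapy alone. The abstract names that shared therapy: "Patients taking Shu-Gan-Jian-Pi Decoction combined with prednisone and azathioprine will be in the case group". Only the decoction differs between the groups.

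The Background says of the shared therapy that it works in most patients, "with alleviation of symptoms achieved in 60 to 80% of cases". One of the three entry routes is "serum aspartate aminotransferase (AST) ≥ 10-fold upper limit of normal (ULN) levels". A second combines a lower AST threshold with raised gammaglobulins, and the third is histological with no AST threshold.

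The Discussion, but not the methods section, promises propensity scores to balance the two groups, which are formed by patient preference.

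**The concern.** The trial asks what the decoction adds to steroid therapy. The pre/post test in the case group uses case-group data only. Those values move with prednisone plus azathioprine and, in patients admitted on a very high AST, with regression to the mean. Any decoction effect is part of the change, but the test has no means of isolating it, because the controls, who show what happens without the decoction, do not enter it. Correct pairing of the test does not alter this.

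Two misreadings are at stake. A significant case-group change could be taken as efficacy of the decoction. Or the two within-group results could be set side by side, and a significant result in one group only could be taken as a difference between groups, which it is not.

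**Working it through.** **Inputs from the article.** 110 evaluable patients at about 1:1, so 55 per group; 132 enrolled (66 per group); 15% dropout; two-tailed 0.05; 60 to 80% symptom alleviation on standard therapy.

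**Assumptions.** The article gives no effect size or SD, so the standardised within-group change is taken over 0.3 to 0.8. The symptom figure stands in for the share of patients whose status changes, and lower values are shown as well. The decoction effect is set to zero unless stated.

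**The plan's own figure.** 55/0.85 = 64.7, rounded up to 65 per group, or 130 in total. This agrees with the stated 132 to within 2 patients, so 55 per group is a fair working number.

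**Step 1: change of status, nobody normal at baseline.** If all changes go one way, the exact McNemar P-value with b changers is 2 × 0.5^b. At b = 5 it is 0.0625; at b = 6 it is 0.031. So six changers suffice, and the rejection probability is P(Bin(n, p) ≥ 6).

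| Share changing status | n = 55 | n = 66 |
|---|---|---|
| 10% | 0.476 | 0.657 |
| 20% | 0.975 | 0.995 |
| 30% | 0.9998 | >0.999 |
| 60% | >0.999 | >0.999 |

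**Step 2: some patients normal at baseline.** With 20% normal before treatment, and the article's Fisher test applied unpaired at n = 55, the rejection probability is 0.560 if 40% are normal afterwards, 0.989 if 60% are, and about 1.000 if 80% are. The result in Step 1 therefore needs few normal values at baseline or a high response.

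**Step 3: continuous laboratory values.** The paired t-test has 54 degrees of freedom and noncentrality d × √55. Its rejection probability is 0.589 at d = 0.3, 0.830 at 0.4, 0.954 at 0.5, 0.992 at 0.6 and 0.9999 at 0.8.

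**Step 4: contrast with the between-group test.** With equal underlying response of 60% or 80% in both groups, a simulation of 200,000 replicates gives a between-group rejection rate of 0.049 to 0.051. This takes the groups as comparable, which patient preference does not guarantee; hence the need for adjustment.

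**Step 5: a harmful decoction.** If the decoction lowered response from 60% to 40%, the case-group test of Step 1 would still be significant with probability above 0.999.

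**Step 6: side-by-side reading.** For two independent groups with the same true change, P(exactly one significant) = 2 × power × (1 − power); half of this falls to the case group.

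| Equal change (SD) | Calculation | Exactly one | Case group only |
|---|---|---|---|
| 0.3 | 2 × 0.589 × 0.411 | 48% | 24% |
| 0.4 | 2 × 0.830 × 0.170 | 28% | 14% |
| 0.5 | 2 × 0.954 × 0.046 | 9% | 4% |
| 0.8 | 2 × 0.9999 × 0.0001 | about 0% | about 0% |

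The two problems sit at opposite ends of the range. Where the single-group test is nearly certain to be significant, discordance vanishes. Where discordance is high, the single-group test is far from certain (0.589 at 0.3 SD).

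**The case against.** The strongest reply is that the harm is hypothetical. The between-group comparison comes first, the pre/post comparison is added to it, and the common threshold comes from general sentences about all P-values. A reader might infer that the trial will claim efficacy from within-group change, or set the two P-values side by side. The article says neither.

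Three other stronger readings also fail. First, a reader might say that the tests do not depend on the decoction at all. They do: case-group values after treatment contain any decoction effect. What the test lacks is a way to separate it. Second, a reader might extend the point to the primary outcome. That outcome combines remission at the last observation visit with absence of steroid side effects throughout the period, so it has no pre-treatment value and no pre/post test. Several secondary outcomes are likewise post-treatment proportions, and near-certain significance is not shown for the safety tests done before and after treatment. Third, a reader might quote 48% as the general error rate. It is close to the ceiling of 50% that the formula allows, and it rests on a 0.3 SD change for which the article gives no basis.

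It is also fair that the 60 to 80% concerns symptoms and not laboratory values, and that the regression argument applies only to patients entering on AST. Finally, replacing P-values by confidence intervals would alone change little: a 95% interval for a mean change excludes zero exactly when the paired t-test gives P<0.05.

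These replies narrow the point. They do not remove it, because the within-group tests are a stated choice and not a detail left to a fuller document, and nothing limits what may be concluded from them.

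**Conclusion.** The concern holds in a limited form. For disease-activity measures, the planned case-group pre/post test cannot distinguish a useful decoction from an inert one, and where background response is high it would be significant even with a harmful one. With an inert decoction its probability of significance at n = 55 is 0.975 or more once 20% change status from an almost wholly abnormal baseline, but only 0.59 at an assumed change of 0.3 SD. Comparing the two within-group P-values would mislead most at small shared changes and hardly at all at large ones. All SD values are assumptions.

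The primary analysis, sample size and data collection are untouched. This is a cheap improvement to the analysis wording, not a flaw that invalidates the trial.

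**What to change.** In the section on sample size and statistical methods:

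- Drop the within-group significance tests, or keep within-group change and label it descriptive.
- State that no conclusion about the decoction will be drawn from within-group change or from comparing within-group P-values. This sentence matters more than whether P-values or intervals are printed.
- State that efficacy conclusions rest on the between-group difference, and carry the propensity-score adjustment from the Discussion into the methods.
- For continuous laboratory variables, replace the plain t-test by a between-group comparison with the baseline value as covariate.

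The cost is fewer P-values to report and slightly more analysis work. No further patients or measurements are needed.

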### Patient population

A total of 132 AIH patients, who fulfill the screening criteria, is being enrolled and followed up between October 2015 and June 2017. According to the patients’ preference, the eligible AIH patients will be divided into two groups: the case group (to receive SGJP Decoction combined with low dose prednisone and azathioprine, *n* = 66) or a control group (to receive low dose prednisone and azathioprine, *n* = 66).

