### Outcome measurements

#### Primary outcome

The primary outcome was complete response to therapy, defined as complete biochemical remission at the patient’s last visit of observation period and the absence of predefined steroid-specific side effects throughout observation period (moon face, central obesity, buffalo hump, diabetes and increased intraocular pressure, etc.). Biochemical remission was defined as complete normalization of aminotransferase levels including IgG.

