## Discussion

AIH is known as a harmful disease with a high mortality which can easily progress to cirrhosis or liver failure. Prednisone plus azathioprine is considered the mainstay of therapy in the current recommendations for AIH therapy originate from this era. However, it does not provide good benefits for AIH patients because of its serious side effects. In this case, TCM has been popular used to treat AIH in China with good efficacy, low costs and small side effects. However, there is no rigorous and objective testing. What is more, Western medicine and TCM approaches have been used together to reach great effect worldwide [15]. Therefore, we conduct this study to explore whether the combination treatment of an empirical Chinese Herbal formula (SGJP Decoction) and steroids standard therapy could improve the clinical management of AIH.

This prospective study aims to explore the efficacy and safety of SGJP Decoction combined with steroid standard therapy on AIH. The achievement of this trial will provide evidence-based data for SGJP Decoction, which could provide good benefits for AIH patients. More over, the success of this study would represent justification and impetus for a large scale clinical study to further consolidate the evidence for the use of SGJP Decoction in AIH patients.

Our study also has several limitations that require consideration. Firstly, the case and control groups are not randomly assigned. However, we will use a new method of statistical analysis to make up for this shortage, the causal inference method, which has been used in previous randomized controlled trials [16]. In this method, propensity scores can balance the case and control group by limiting the confounding factors so that can help researchers to evaluate the interventions more accurately. Secondly, the sample size is still too small. However, the study produced critical data for sample size calculation of future study. And control of confounding variables, appropriate randomization, sufficient sample size and longer treatment period should be included in future study.

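### Groups are formed by patient preference, yet the Methods give only unadjusted tests and the Discussion promises propensity scores; neither analysis is named as primary for complete response

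*Protocol article*

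**What the plan says.** The protocol article describes the design plainly under Study design: "This is a prospective, non-randomized, controlled study". Under Patient population, allocation follows the patients' "preference, the eligible AIH patients will be divided into two groups", with 66 patients planned in each.

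The primary outcome is binary: biochemical remission at the last visit of the observation period, together with no predefined steroid-specific side effects.

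Under Sample size and statistical methods, the analysis is set out as follows: "Comparisons will be conducted between the case group and the control group, also between pre-treatment and post-treatment in each group". The tests named are two-tailed t-tests for normally distributed variables and Pearson chi-squared or Fisher exact tests for the others, with P below 0.05 as significant. A binary outcome therefore gets a crude chi-squared or Fisher test. The section mentions no covariate, matching, weighting, stratification or propensity score.

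The limitations paragraph of the Discussion adds a second analysis: "we will use a new method of statistical analysis to make up for this shortage, the causal inference method". It explains in general terms that propensity scores can balance the groups. A few sentences later it says that "control of confounding variables, appropriate randomization, sufficient sample size and longer treatment period should be included in future study".

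**The concern.** When patients choose their treatment, the groups may differ in prognosis before treatment starts. The article makes this a concrete possibility. Its Background says that patients turn to Chinese medicine because of recurrence and corticosteroid side effects. Its inclusion criteria admit both first-diagnosis and relapsed patients, through three alternative treatment indications. The primary outcome is remission without steroid side effects, so the stated reasons for choosing the herbal treatment bear on both halves of it. Equal group sizes do not remove this, and neither do the pre-post tests within each group.

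Two things are at stake. If the Methods section is followed literally, the crude difference mixes the effect of the decoction with differences between the kinds of patients who choose it, and its 5% error rate is not assured. If both analyses are run and disagree, nothing in the article says which one counts. The Conclusions section expects the study to verify a benefit that would support wide use, so the rule for deciding the primary result needs to be fixed beforehand.

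**Working it through.** **Setting the statements side by side**

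| Place in the protocol article | What it commits to |
|---|---|
| Patient population | Groups formed by patient preference |
| Sample size and statistical methods | Crude t, chi-squared and Fisher tests, P < 0.05 |
| Discussion, limitations | A propensity-score analysis will be used |
| Discussion, end of the same paragraph | Confounder control listed for a future study |

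No statement links the propensity score to complete response, and none ranks the two analyses.

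**What the documents supply for a calculation**

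They give 110 evaluable patients, so 110/2 = 55 per group, and 132 enrolled, so 66 per group. The enrolment figure is roughly consistent with its stated basis: 110/(1 − 0.15) = 129.4, or 130, against 132. They give no response rate, no prognostic effect and no expected imbalance. Everything below is therefore an illustration on assumed values.

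**Illustration**

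Assume no treatment effect and one binary factor (for example relapse), with response 40% if present and 70% if absent. Suppose the factor is commoner in the decoction group, as the Background would suggest for relapse.

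*Case A, factor in 50% of the decoction group and 30% of controls*
- Decoction: 0.5 × 0.40 + 0.5 × 0.70 = 0.55
- Control: 0.3 × 0.40 + 0.7 × 0.70 = 0.61
- Spurious difference: 0.55 − 0.61 = −0.06
- Null SE, pooled p = 0.58: √(2 × 0.58 × 0.42/55) = 0.0941
- Actual SE: √((0.55 × 0.45 + 0.61 × 0.39)/55) = 0.0939
- Probability of a significant result against the decoction: Φ((0.06 − 1.96 × 0.0941)/0.0939) = 0.093
- Probability of a significant result in its favour: Φ((−0.06 − 1.96 × 0.0941)/0.0939) = 0.005
- Total: about 9.7%

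*Case B, factor in 60% and 30%*
- Decoction: 0.6 × 0.40 + 0.4 × 0.70 = 0.52; control 0.61; difference −0.09
- The same formulas give 0.156 against and 0.002 in favour, about 15.7% in total.

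Exact enumeration of the Pearson chi-squared test with binomial outcomes, 55 per group:

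| Case | Total rejection | Decoction falsely worse | Decoction falsely better |
|---|---|---|---|
| A | 9.4% | 9.0% | 0.4% |
| B | 15.1% | 15.0% | 0.2% |

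If the factor were instead commoner among controls, the last two columns would swap.

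**Range over other assumed values**

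With 55 per group, overall response 50% and no true effect, the bias equals imbalance × effect of the factor. Rejection rates use the normal approximation.

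| Imbalance | Effect of factor | Bias | Rejection |
|---|---|---|---|
| 10 points | 20 points | 2 points | 5.5% |
| 20 points | 30 points | 6 points | 9.6% |
| 30 points | 40 points | 12 points | 24% |
| 40 points | 40 points | 16 points | 39% |

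More patients do not help: at 66 per group the second and third rows become 10.6% and 28%. An analysis that fully balanced the factor would return to about 5%.

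**The case against.** The strongest reply is that adjustment is already planned. The Discussion commits to propensity scores in the future tense, and a journal article may leave covariates, weighting or matching, and balance checks to a fuller document. The sentence about a future study can be read as a wish for better control by design, not as withdrawal of the promise. The article also admits non-randomisation and small size as limitations and looks ahead to confirmatory studies.

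Much of this stands. Missing detail about the score is not the point here, and the future-study sentence alone proves little. What remains is that the section headed as the statistical methods states a different analysis from the Discussion, and the article does not say which is primary.

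A reader might infer more: that the plan contains no adjustment, or that the primary comparison is confounded. The documents support neither. The Discussion does state an adjusted analysis, and since no primary analysis is named, the crude one cannot be presumed to be it. Nor do the documents show a bias towards the decoction. In the illustration with relapse commoner in that group, the excess error falls almost wholly on the side of false harm. Several factors together could add up or offset one another.

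**Conclusion.** The point holds in this form: two analyses that can disagree are stated, neither is designated as primary for complete response, and the one in the Methods leaves a preference-based comparison open to confounding. This is an inconsistency within the article, not a detail left to an unseen analysis plan.

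The illustrated distortions (biases of 2 to 16 points, rejection rates of 5.5% to 39% against a nominal 5%) rest entirely on assumed prognostic effects and imbalances. They show what the crude test could do, not what it will do. The claim that a statistical method offsets the absence of randomisation is also too strong, because propensity scores balance only measured factors.

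The matter should be settled before analysis because it governs how the primary result is obtained. The article describes recruitment as ongoing, so at that stage there was time to do so.

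**What to change.** 1. Move the promised propensity-score analysis into the statistical methods and name it as the primary analysis of complete response, reported as an adjusted difference with a 95% confidence interval.
2. Prespecify a short list of baseline covariates that the entry criteria, outcomes and planned pre-post comparisons already call for, such as first diagnosis versus relapse, AST, IgG, TBIL and age. About 110 evaluable patients will not support a long list. The article does not show that items such as BMI or prior steroid exposure are recorded, so the plan should not count on them without checking.
3. State how the score will be used, and report covariate balance before and after adjustment.
4. Label the unadjusted tests descriptive.
5. In the Discussion, replace the wording that the method compensates for non-randomisation with a statement that only measured confounders are adjusted for, and make the future-study sentence consistent with the adjustment planned here.

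The cost is some redrafting, a little more analysis work and possibly a wider confidence interval. With the covariates suggested, no additional patients are needed.

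### The stated test rule sends non-normal variables to chi-squared or Fisher tests and names no paired test for before/after categorical data; the form of the primary test is not affected

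*Protocol article*

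**What the plan says.** All of the following is in the protocol article.

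- **Comparisons planned** (Sample size and statistical methods): "Comparisons will be conducted between the case group and the control group, also between pre-treatment and post-treatment in each group".
- **Summaries** (same section): "Data will be presented as mean and standard deviation, or frequency and percentages". No median or range is mentioned.
- **Tests** (same section): "For normally distributed variables, means will be compared by using t-tests (two-tailed"), and then "nonparametric variables will be analyzed using Pearson chi-squared tests or Fisher exact tests". No other test is named, and the rule does not separate between-group from before/after comparisons.
- **Threshold** (same section): "A P-value of less than 0.05 will be considered statistically significant", two-tailed, for all comparisons alike.
- **Primary outcome**: "The primary outcome was complete response to therapy, defined as complete biochemical remission at the patient’s last visit of observation period", together with freedom from listed steroid side effects. This is a yes/no outcome.
- **Secondary outcomes**: all are proportions or rates.
- **Safety outcomes**: blood, urine, stool and renal function tests and the electrocardiogram are taken in the same patients before and after treatment.

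**The concern.** The rule sets normally distributed variables against *nonparametric* ones. Read literally, the second class is continuous data that are not normal. A chi-squared or Fisher test cannot be run on such data unless they are first cut into categories, and the rule gives no cut-points for laboratory values outside the defined outcomes.

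The rule also has to serve the comparisons "also between pre-treatment and post-treatment in each group". Each patient then contributes two linked observations, but both categorical tests named assume independent samples.

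This is more than a detail left for an analysis plan. The text makes a positive assignment that is wrong, and a later plan naming suitable tests would contradict it. At stake are the before/after categorical comparisons (for example, a normal or abnormal safety test, or a symptom present or absent) and any non-normal laboratory values. A change in a safety measure could be missed because the test is less sensitive than it need be.

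**Working it through.** **The plan's own figures.** No figure in the article depends on the choice of test. The 110 evaluable patients come from expert consensus, with no effect size or power. Allowing 15% dropout gives 110 / (1 − 0.15) = 129.4, so 130, close to the stated 132. The check below uses 110 / 2 = 55 per group.

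**Step 1: match each data type to the rule.**

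| Data | Test the rule gives | Suitable in form? |
|---|---|---|
| Between groups, normal continuous | t-test | Yes |
| Between groups, categorical (primary and secondary outcomes) | chi-squared or Fisher | Yes |
| Between groups, non-normal continuous | chi-squared or Fisher (literal reading), or none (if *nonparametric* means categorical) | No |
| Before/after, normal continuous | t-test, form not stated | Yes, if paired |
| Before/after, non-normal continuous | as for between groups | No |
| Before/after, categorical | chi-squared or Fisher | No: independence fails |

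The last row fails on either reading of *nonparametric*.

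**Step 2: size of the before/after categorical error.** The article gives no within-patient correlation, so a range is assumed: latent normal correlation ρ of 0.3, 0.5 and 0.7. Half the patients are assumed positive at each time under the null. There are 55 pairs, a two-sided 0.05 level and 20,000 simulated trials per row. Power is for an assumed latent shift of 0.5 SD.

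| ρ | Size, unpaired chi-squared | Size, McNemar | Power, unpaired chi-squared | Power, McNemar |
|---|---|---|---|---|
| 0.3 | 0.026 | 0.053 | 0.54 | 0.63 |
| 0.5 | 0.016 | 0.052 | 0.54 | 0.70 |
| 0.7 | 0.006 | 0.045 | 0.54 | 0.80 |

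*Analytic check.* With half the patients positive, the correlation of the two binary values is φ = (2/π) arcsin ρ. The unpaired test overstates the variance of the difference by a factor 1/(1 − φ), so its size is about 2[1 − Φ(1.96/√(1 − φ))].

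- ρ = 0.3: φ = 0.194, 1.96/√0.806 = 2.18, size 0.029
- ρ = 0.5: φ = 0.333, 1.96/√0.667 = 2.40, size 0.016
- ρ = 0.7: φ = 0.494, 1.96/√0.506 = 2.75, size 0.006

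These agree with the simulation to within 0.003. The error is conservative.

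**Step 3: before/after means, only if the t-test were run unpaired.** The article does not say that it would be. The size is 2[1 − Φ(1.96/√(1 − ρ))], with ρ now the correlation of the measurements.

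- ρ = 0.3: 1.96/√0.7 = 2.34, size 0.019
- ρ = 0.5: 1.96/√0.5 = 2.77, size 0.006
- ρ = 0.7: 1.96/√0.3 = 3.58, size 0.0003 (simulation 0.0006)

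For an assumed change of 0.4 SD at ρ = 0.5, simulated power is 0.56 unpaired and 0.83 paired. Size exceeds 5% only with negative correlation (0.075 at ρ = −0.2), which is not expected for repeated measurements in one patient.

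**Step 4: using the t-test on skewed data instead.** For between-group log-normal data with log-SD 0.5, 1.0 and 1.5 (assumed), the simulated size of the t-test at 55 per group is 0.049, 0.042 and 0.035. This fallback would not produce excess false positives either.

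**The case against.** The strongest reply is that *nonparametric* is loose wording for categorical. The summary sentence offers only two data types, means with standard deviations and frequencies with percentages, and the two test families follow the same pairing. The laboratory efficacy outcomes are already yes/no at stated thresholds (normalisation, or a fall of more than 50%), and no continuous efficacy outcome is defined. This is a fair reading and it narrows the point. It does not remove it: no rank test would then be named for skewed laboratory values, and the before/after categorical data would still go to tests for independent samples.

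Three stronger inferences are tempting, but the document does not support them.

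- *That all p-values will be invalid.* The primary and secondary outcomes suit chi-squared or Fisher tests between groups. Confounding from allocation by patient preference is a separate matter. Where the paired error does arise, it makes p-values too large, not falsely small.
- *That before/after means will be tested as independent samples.* The article says only t-tests, and a paired t-test is one. Omitting the word *paired* is ordinary condensation, so Step 3 above is conditional.
- *That efficacy will be claimed from within-group change.* The case-versus-control comparison is listed first, and the Discussion describes propensity scores to balance the groups. What remains is that the within-group tests share the same significance threshold and are not marked as descriptive. Both groups receive a background therapy that the Background section credits with relieving symptoms in 60 to 80% of cases, so improvement in both is expected whatever the decoction does.

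**Conclusion.** The point holds in limited form. The stated rule is wrong for non-normal continuous data on its literal reading and silent on them on the lenient one. On both readings it is wrong for before/after categorical data. For the latter, the true size falls to about 2.6% at a latent correlation of 0.3 and 0.6% at 0.7, and power is about 54% where McNemar's test has 63% to 80%. These figures rest on assumed correlations, an assumed 50% starting proportion, an assumed shift and 55 pairs; none of the correlations or effect sizes is in the article. The direction, conservative with lost power, holds for any positive correlation.

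The form of the primary test is sound. Severity is minor to moderate.

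**What to change.** Replace the sentence that assigns the tests with a rule of this kind:

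- Categorical data between groups: Pearson chi-squared or Fisher exact test.
- Non-normal continuous data between groups: Mann-Whitney test, or a t-test after log transformation.
- Before/after continuous data: paired t-test or Wilcoxon signed-rank test.
- Before/after binary data: McNemar's test.
- Within-group changes are descriptive; efficacy conclusions rest on the between-group comparison of the stated outcomes.

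The binary primary outcome stays as it is; moving efficacy to an adjusted analysis of continuous week-24 values would displace it and is not needed to cure this error.

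The cost is one short paragraph of text. The tests are available in SPSS, the package already named. No sample size changes, because none was derived from a test.
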